## Abstract

**Background:** Due to limited time windows and technical requirements, only a small percentage of patients can receive reperfusion therapy for acute ischemic stroke (AIS). Previous studies have shown that LongShengZhi (LSZ) capsule can improve neurological outcomes in patients after AIS, yet those results have not been finally verified through rigorous randomized controlled trials. Thus, this trial was designed to further clarify the efficacy and safety of LSZ capsule for patients with AIS.

**Methods:** LSZ capsule on Functional Recovery after Acute Ischemic Stroke (LONGAN) trial is a prospective, multicenter, randomized, placebo-controlled, double-blind, parallel-group, superiority trial that enrolls patients from stroke and rehabilitation units in China. We will enroll 1,376 patients aged 18 years or older with AIS within 7 days of symptom onset and a National Institute of Health Stroke Scale (NIHSS) score of 4–15. Eligible patients will be randomized to receive either 2 g LSZ capsules three times a day or placebo LSZ capsules for 90 days. The primary outcome is the proportion of patients with favorable outcomes, as measured by the modified Rankin Scale (mRS) 90 days after randomization. The main safety outcome is the proportion of severe adverse events.

**Conclusion:** This study will be the first randomized, double-blind trial to evaluate the efficacy and safety of LSZ capsule in patients with AIS. In order to improve the transparency and reproducibility of the trial, the data will be analyzed in accordance with this pre-specified plan for statistical analysis to reduce bias due to selective analysis and reporting. This trial aims to provide high-quality evidence for the efficacy and safety of LSZ capsule for AIS.

## 1 Introduction

Stroke is a common disease affecting a quarter of the world’s population and the leading cause of death and disability (Feigin et al., 2018). Ischemic stroke (IS), accounting for 70% of strokes, is the most prevalent type of stroke and occurs mainly due to decreased cerebral blood flow caused by thrombosis or embolism (Wang et al., 2017). Current treatments for acute ischemic stroke (AIS) include reperfusion and antiplatelet therapy, as well as admission to the stroke unit. Reperfusion treatment, including intravenous thrombolysis and mechanical thrombectomy, resulted in good prognoses for about 30%–46% of patients (Goyal et al., 2016; Saver et al., 2016; Thomalla et al., 2020). Recombinant tissue plasminogen activator (r-tPA) is an approved primary treatment for AIS. Unfortunately, only a small proportion of patients can undergo reperfusion treatment due to the limited time window and technical requirements. Improvement of the neurological function of patients with AIS remains the main focus and is a difficult issue in clinical practice (Chamorro et al., 2016). During the past 2 decades, many neuroprotective agents have shown promising results in animal experiments, but whether they can be translated to clinical trials is still uncertain (Gladstone et al., 2002; O’Collins et al., 2006; Xu J. et al., 2021). To date, there are no guideline-approved pharmacotherapies for neuroprotection after AIS. Promotion of nerve function recovery remains one of the most important therapeutic strategies for AIS; thus, more appropriate and effective medication options are urgently needed for the improvement of neurological function after AIS.

Chinese medicine (CM), a unique and complicated medical system, has been developed over thousands of years and is widely applied as a supplementary and complementary therapy to Western medicine in IS treatment. Some studies have already provided evidence of potential anti-inflammatory and neuroprotective effects of natural medicines (Xiong et al., 2018; Yang et al., 2020). The LongShengZhi (LSZ) capsule, a well-known traditional Chinese herbal medicine product for treating IS (Chang et al., 2016), is formulated through the modification of a representative prescription (Buyang Huanwu decoction) proposed by Wang Qing-ren during the Qing dynasty. The LSZ capsule was manufactured by Buchang Pharmaceutical Co., Ltd. (Shaanxi, China) and certified as compliant with good manufacturing practices and approved for the treatment of IS in 2001 by the Sino Food and Drug Administration. The LSZ capsule contains 12 natural medicines and 19 main active ingredients (see Supplementary Material). Many of the bioactive ingredients have neuroprotective effects; for example, paeoniflorin, one of the main components, has been proven to suppress oxidative stress and protect neurons (Zhong et al., 2015). Moreover, other studies have indicated that the LSZ capsule has anti-inflammatory and neuroprotective effects and can reduce the activation of platelets and endothelial cells (Li et al., 2019; Yang et al., 2020). Network pharmacology can be used to predict and identify the potential active component of herbal medicine (Xu et al., 2021; Zhang et al., 2022). Based on a network pharmacology analysis, the LSZ capsule can regulate the pathological process of IS through the modulation of inflammation processes, trophic factor secretion, and immune-related lymphocyte regulation (Sun et al., 2019). Also, the main active ingredients of ″Persicae Semen - Carthami Flos - Chuanxiong Rhizoma″ drug group could form a better docking mode and high affinity with extracellular signal - regulated protein kinase 2 (ERK2) and Janus kinase 2 (JNK2), which had a good activity of treating stroke (Xu et al., 2019a; Xu et al., 2022). Previous clinical reports have demonstrated that the LSZ capsule can prevent atherosclerosis and improve the prognosis and nerve function in IS (Liu, 2014). Additionally, it has been reported that LSZ can reduce Alzheimer’s disease (AD) Aβ plaque accumulation by inhibiting relative gene expression and significantly improve the cognitive performance of mice without increasing the incidence of adverse effects (Yin et al., 2020).

However, the current clinical studies of LSZ lack high-quality evidence and have been limited by methodology, sample size, and non-hard outcome indicators like symptom improvement. Futhermore, the well-documented and transparent statistical analysis is indispensable to reduce publication bias, prevent selective analysis and reporting of research outcomes and support reproducibility, given the influence of statistical decisions on study conclusion. Therefore, we have designed a large-scale, multicenter, double-blind clinical trial to determine the efficacy and safety of the LSZ capsule in patients after AIS (LONGAN). In this paper, we summarized the protocol and statistical analysis plan (SAP) for the primary analysis of LONGAN in accordance with both the Standard Protocol Items: Recommendations for Interventional Trials (SPIRIT) guidelines and the corresponding reporting guideline for SAPs (Chan et al., 2013; Gamble et al., 2017).

## 2 Methods and design

### 2.1 Study design and patient selection

The LONGAN trial is a prospective, multicenter, randomized, placebo-controlled, double-blind, parallel-group, superiority trial that enrolls patients from stroke and rehabilitation units in China. This study will be conducted at 15 sites across China. The primary objective of the trial is to test the hypothesis that LSZ capsule is superior to the placebo for increasing the proportion of favorable functional status, defined as a modified Rankin Scale (mRS) score ≤1 at 90 days. The secondary objective is the assessment of any other benefits or harms from the end of the treatment period up to 180 days after the stroke. Participants will be followed up at 30, 90 and 180 days after randomization (D30, D90 and D180, respectively) to collect efficacy and safety outcomes in person. Patient enrollment will begin in May 2022 and end in June 2023. Figure 1 presents a schematic diagram of the patient timeline. The trial was approved by the institutional review board of Dongzhimen Hospital, Beijing University of Chinese Medicine, Beijing, China and registered in public clinical trial database (No. 2021DZMEC-198-02; ClinicalTrials.gov Identifier NCT 05277311). We described this study protocol according to the SPIRIT 2013 Statement, and the complete checklist is available.

**FIGURE 1 F1:**
[figure not shown]
The schematic diagram of the patient timeline.

All patients admitted for a course of inpatient rehabilitation following AIS will be recruited and screened for eligibility based on inclusion and exclusion criteria in the study. Also, the study will be advertised on posters in these medical centers, allowing patients to voluntarily contact investigators. Patients will be further screened for study eligibility for AIS treatment through standard admission assessments: comprehensive medical, neurological, and psychiatric histories; reviews of medical records; physical and neurological examinations; reviews of brain imaging reports and electrocardiogram; and pregnancy test only for the premenopausal women. Furthermore, registration data for eligible patients will be collected. Logs of all patients excluded from the study will be retained to document the reasons for exclusion. Screening logs will be submitted to the coordination center monthly. Eligible patients will be informed of the risks and benefits of the study by trained research clinicians. If they agree to participate in the study, patients and/or their legal surrogates will provide written informed consent forms. The intervention will be initiated as soon as possible after randomization. The detailed diagnostic criteria, inclusion and exclusion criteria are presented in Table 1.

**TABLE 1 T1:** Inclusion and exclusion criteria of the LONGAN trial.

Inclusion criteria
Acute ischemic stroke patients within 7 days of onset
18 years of age or older, and gender not limited
NIHSS score of 4–15 at randomization
**Exclusion criteria**
Secondary stroke caused by a tumor, traumatic brain injury, hematological disease, or other diseases with a confirmed diagnosis
Pre-stroke mRS score of more than 1
Known severe liver or kidney dysfunction
Known allergies for ingredients in the investigational product
Known bleeding diathesis or coagulation disorder
Known medical condition likely to limit survival to less than 3 months
Pregnant women (clinically evident) or breastfeeding women
Participation in any investigational study in the previous 3 months
Known dementia, uncontrolled psychiatric problems
Any condition that could impose hazards to the patient if study therapy is initiated or affect the participation of the patient in the study. The judgment is left to the discretion of the investigator

NIHSS, national institute of health stroke scale; mRS, modified Rankin Scale.

### 2.2 Randomization, allocation, and blinding

Eligible patients who consent to participate will be assigned to the LSZ capsule experimental or control group at a 1:1 ratio using permuted block randomization stratified according to medical centers. The randomization program will be generated by an independent statistician using SAS software v9.4 (SAS Institute, Inc.; Cary, NC, United States) and stored in sealed, sequential, opaque envelopes. The site pharmacist will retain these envelopes, which will be assigned in the order specified by the statistician.

At randomization, study medications will be packaged into a large box containing LSZ capsules or LSZ placebo capsules. When the patient is discharged, the trial medication will be continued and documented on the discharge summary and on the patient’s list of ongoing medications. At 30 days after randomization, patients will be instructed to bring partial empty boxes to this follow-up. Patients who stop taking the allocated treatment early will be followed up, and their data will be included in the primary analyses. The reason for stopping the treatment prematurely, e.g., a SAE, will be recorded in the patient’s electronic case report form (CRF).

Active and placebo capsules with identical appearances, colors, and flavors will be prepared by Buchang Pharmaceutical Co, Ltd. The placebo capsules are visually identical to the LSZ capsules, even when broken open. In the study, each patient’s medications will be prepared as a unit-dose kit according to the predetermined randomization schedule. The site pharmacies will not disclose the randomization assignments unless information is required for patient treatment in exceptional circumstances. The clinical center pharmacist will be unblinded to the treatment, but all investigators, participants, caregivers, and data analysts will be blinded to treatment assignments throughout the trial until the blind codes are revealed. Investigators can request emergency unblinding in cases of serious adverse events (SAEs) suspected to be associated with the investigational medicine.

### 2.3 Treatment

Eligible patients will be randomly assigned to the experimental and control groups. Participants in the experimental group will receive 5 LSZ capsule (0.4 g each), three times a day for 90 days. The control group will receive a LSZ placebo using the aforementioned protocol; the main ingredients of placebo including starch, dextrins, silicon dioxide, medical yellow iron oxide, caramel color liquid, and purified water will be identical to the LSZ capsule in appearance, weight, and taste. The treatment assignments are presented in Figure 2. All patients will receive a standard treatment, which is referred to in the current guidelines (Chinese Society of Neurology and Chinese Stroke Society, 2018; Powers et al., 2019), including antiplatelet therapy, control of vascular risk factors, and appropriate rehabilitation. During the trial, drugs with composition or efficacy similar to the study drug, such as CM decoctions (compound granules), CM injections, and Chinese patent medicine and health products, will not be permissible. Other concomitant medications will be allowed during the study, but these should be recorded in the subjects’ CRF during the trial. The study drug will be discontinued in cases of SAEs, request for study withdrawal by the patient or their legally authorized representative, or poor compliance or non-adherence to the prescribed interventions. We will truthfully record the reasons for stopping interventions.

**FIGURE 2 F2:**
[figure not shown]
The flowchart of the LONGAN trial. IS, ischemic stroke; mRS, modified Rankin Scale; NIHSS, National Institute of Health Stroke Scale; FMMS, Fugl–Meyer Motor Scale; MoCA, Montreal Cognitive Assessment; BI, Barthel Index; EQ-5D, EuroQol-5D Questionnaire; LSZ, LongShengZhi;HR-MRI, high-resolution magnetic resonance; MR, magnetic resonance.

### 2.4 Efficacy outcomes

The primary outcome will be the proportion of patients with a favorable outcome, which is defined as mRS ≤1 on D90 (Rankin, 1957). The mRS is an ordinal scale ranging from 0 to 6 (Lees et al., 2012), with 0–1 indicating no disability, 2 to 5 indicating disability (increasing from 2 to 5), and 6 indicating death. The secondary outcomes will be as follows: 1) distribution of mRS scores [will be measured on D30 and D90]; 2) proportion of patients with good functional status [defined as mRS score ≤2; will be measured on D30 and D90]; 3) neurological deficit improvement [defined as a change in the National Institute of Health Stroke Scale (NIHSS) score (Brott et al., 1989), ranging from 0 to 42, with higher scores indicating more severe strokes; will be measured at baseline, D30, and D90]; 4) proportion of poor health-related quality of life (poor-HRQOL) [available EuroQol-5D Questionnaire (EQ-5D) data will be used to calculate EQ-5D index scores (Dorman et al., 1997). Poor-HRQOL is defined as an EQ-5D index score ≤0.5 and will be measured on D30 and D90. The EQ-5D index score is measured on a scale between 0 (death) and 1 (full health). The patient’s mobility, self-care ability, daily activities, feelings of pain or discomfort, and feelings of anxiety or depression contribute to EQ-5D. Here, each aspect will be divided into three levels (Rabin and de Charro, 2001): no problems, moderate problems, or extreme problems. The EQ-5D index score (preference-based health status) will be determined using the population-based preference weight values for five dimensions of the scale (Dolan, 1997; Shaw et al., 2005; Liu et al., 2014). This study will use preference weights applicable to the Chinese population (Liu et al., 2014)]; 5) proportion of patients with functional independence [defined as Barthel Index (BI) ≥90 (Mahoney and Barthel, 1965); BI is a conventional scale used to assess the activities of the daily living of stroke patients involving 10 items with a maximum score of 100 points; will be measured on D30 and D90]; 6) changes in motor function [measured by the Fugl–Meyer Motor Scale (FMMS) score (Fugl-Meyer et al., 1975), ranging from 0 to 100, with lower scores indicating poorer motor status; the change from baseline of the FMMS will be measured on D90]; and 7) changes in cognitive function [measured by the Montreal Cognitive Assessment (MoCA) score (Nasreddine et al., 2005), ranging from 0 to 30, with less than 26 indicating cognitive impairment; the change in MoCA from baseline will be measured on D90].

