### 2.12 Statistical analysis plan

#### 2.12.1 Full analysis set

Statistical analysis will be conducted by a third-party statistical unit using SAS v9.4 software (SAS Institute, Inc.). The full analysis set (FAS) will be the data set as close as possible to the ideal set of subjects in compliance with the intention-to-treat principle, and all subjects who are randomized into the group and have more than one medication record and evaluation of its efficacy will be included in the FAS. Missing data will be imputed using the last observation carried forward (LOCF) method if there are efficacy values after randomization. The FAS will be used for primary efficacy analysis in this study, and all efficacy variables will be analyzed using the FAS.

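### The LOCF rule in 2.12.1 has no exception for death, so a patient who dies between D30 and D90 can count at D90 as functionally independent and as not having poor quality of life

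*Protocol article*

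**What the plan says.** All references are to the protocol article.

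- **Missing data (2.12.1).** "Missing data will be imputed using the last observation carried forward (LOCF) method if there are efficacy values after randomization". The same section says that "all efficacy variables will be analyzed using the FAS", so the rule reaches the secondary scales. Entry to the FAS requires that subjects "have more than one medication record and evaluation of its efficacy will be included in the FAS". Death is not mentioned.
- **Visits (2.7).** The mRS, NIHSS, FMMS, MoCA, BI and EQ-5D are all assessed at 30, 90 and 180 days. D30 is therefore the only scheduled post-randomisation visit before D90.
- **Barthel Index (2.4).** Functional independence is "defined as Barthel Index (BI) ≥90", at D30 and D90. No value is given for death.
- **EQ-5D (2.4).** "available EuroQol-5D Questionnaire (EQ-5D) data will be used to calculate EQ-5D index scores". The cut-off is stated as "Poor-HRQOL is defined as an EQ-5D index score ≤0.5 and will be measured on D30 and D90", and the scale runs from 0 for death to 1 for full health.
- **mRS (2.4).** The scale has its own category for death: "and 6 indicating death".
- **NIHSS, FMMS and MoCA (2.4).** Ranges are given, but no value for death.

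**The concern.** Death is a known outcome, not an unobserved score. A rule that fills every empty D90 field with the last living value can place a patient who has died in the favourable category of two secondary outcomes. That patient is at the same time in the worst category of the mRS, so the trial would report contradictory results for one person at one visit. For EQ-5D the result also conflicts with the plan's own scale, on which death lies below the poor-HRQOL cut-off.

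These outcomes are tested at two-sided p<0.05 (2.12.5). If mortality differed between arms, the rule would hide part of that difference in the BI and EQ-5D comparisons. If the handling of death is settled only once the data are in view, the pre-specification that the article promises is weakened.

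**Working it through.** **Step 1. Follow the written rules for one patient.** Take a patient with BI 95 and EQ-5D index 0.7 at D30 who dies on day 60.

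| Outcome at D90 | Rule that applies | Result |
|---|---|---|
| mRS ≤1, mRS ≤2, mRS distribution | Death is mRS 6 (2.4) | Failure; worst category |
| BI ≥90 | No D90 value; D30 value carried (2.12.1) | 95, independent |
| EQ-5D index ≤0.5 | No D90 questionnaire; D30 value carried (2.12.1) | 0.7, not poor-HRQOL |
| EQ-5D index, by its own anchor | Death is 0 (2.4) | 0 ≤ 0.5, poor-HRQOL |
| NIHSS, FMMS, MoCA change | D30 value carried (2.12.1) | Living score past death |

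A patient who dies on day 20 may still enter the FAS through an mRS of 6, but has no post-randomisation BI or EQ-5D value to carry. That patient may drop out of those comparisons.

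**Step 2. Is there a plan figure to reproduce?** Not on this point. The article gives no mortality rate and sizes no scale outcome. The only stated figures are for the primary outcome: 1,238 evaluable, and 1,238 / 0.90 = 1,375.6, so 1,376 recruited. Neither is affected. Half of 1,238, that is 619 per arm, is used below.

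**Step 3. Illustrate the size for BI ≥90 at D90.** All of these inputs are assumptions: deaths by D90, d = 2–6%; share of deaths after D30, f = 30–70%; share of those later deaths with BI ≥90 at D30, q = 10–50%; 65% of survivors independent; deaths before D30 drop out.

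- Deaths D = N·d; late deaths L = D·f; early deaths E = D − L.
- Independent survivors I = 0.65·(N − D).
- Death counted as failure: I / N.
- As written: (I + L·q) / (N − E).
- Dead patients counted as independent: L·q.

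Middle case (d 4%, f 50%, q 30%): D = 24.76, L = E = 12.38, I = 0.65 × 594.24 = 386.26, L·q = 3.7.

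- Death as failure: 386.26 / 619 = 0.624.
- As written: (386.26 + 3.71) / 606.62 = 0.643.
- Of the 1.9-point gap, carrying scores forward accounts for 3.71 / 619 = 0.6 points. Losing the early deaths from the denominator accounts for the remaining 1.3.

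| d | f | q | Dead counted independent, per arm | Death as failure | As written |
|---|---|---|---|---|---|
| 2% | 30% | 10% | 0.4 | 0.637 | 0.647 |
| 4% | 50% | 30% | 3.7 | 0.624 | 0.643 |
| 6% | 70% | 50% | 13.0 | 0.611 | 0.644 |

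Over the whole grid the arm proportion is 0.627–0.649 as written, against 0.611–0.637 with death as failure.

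**Step 4. Between-arm effect** (f 50%, q 30%, the same 65% among survivors in both arms).

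- Deaths 6% vs 2%. Death as failure: 378.21/619 − 394.30/619 = 0.611 − 0.637 = −2.6 points. As written: 383.78/600.43 − 396.16/612.81 = 0.639 − 0.646 = −0.7 points.
- Deaths 4% vs 2%: −1.3 points against −0.4 points.
- Equal mortality, with equal f and q: zero under both rules.

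**The case against.** The best case on the other side has four parts.

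1. **The article condenses a fuller plan.** Scale-by-scale scoring of death is commonly left to a full SAP, which is not shown. That would answer a complaint about missing detail. It does not answer a stated LOCF rule that covers all efficacy variables and, followed as written, gives a wrong classification.
2. **A known death need not be treated as missing data.** For EQ-5D, applying the anchor of 0 is at least as natural as carrying a living score. This is fair, and it may be what the sponsor intends. But no sentence says so, and for BI there is no anchor to fall back on.
3. **The effect is small and only secondary scales are touched.** Both statements are probably right. Function including death is already reported through the mRS at D30 and D90.
4. **Worst-rank scoring for NIHSS, FMMS and MoCA changes the estimand.** Statisticians reasonably differ on this, and a while-alive analysis is a legitimate alternative. This part of the objection stands in full.

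A reader might also infer from "available EuroQol-5D Questionnaire (EQ-5D) data will be used to calculate EQ-5D index scores" that all the secondary scales are analysed in survivors only, so that preventing deaths could make the treated arm look worse. The text does not support that. The word *available* is used of EQ-5D alone, in a description of how the index is calculated, and *only* does not appear. Under 2.12.1, a death after D30 with a D30 value is imputed and stays in the analysis, so at most the deaths before D30 drop out.

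**Conclusion.** The point holds in a limited form. As written, the LOCF rule in 2.12.1 lets a patient who dies between D30 and D90 count at D90 as functionally independent and as not poor-HRQOL. This contradicts mRS 6 for the same patient and the plan's own EQ-5D anchor. The source is 2.12.1, not the EQ-5D wording in 2.4.

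The size cannot be derived from the document. The counts and between-arm differences above rest wholly on assumed mortality, timing of death and D30 scores. They indicate a small effect unless mortality differs between arms. The primary outcome and the other mRS outcomes are not affected for known deaths, and no sample size changes. Nor can it be said that every scale already classifies death: only the mRS and EQ-5D carry a stated value for it.

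**What to change.** In 2.12.1, state that LOCF does not apply after death. State also that from death onward a patient counts as not functionally independent (BI <90) and as poor-HRQOL (EQ-5D index 0), including patients who die before D30. Add a cross-reference in 2.4.

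For NIHSS, FMMS and MoCA, state that no living score is carried past death, and name the chosen handling in advance. Worst rank or a while-alive analysis is the sponsor's choice; worst rank would need the rank-based test that 2.12.5 already lists as an option.

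The cost is a few sentences. No new data are needed, because deaths are already recorded as mRS 6. The one downside is that the two binary outcomes become death-inclusive; a survivors-only result can be shown as supportive.
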